### 3.4 Relevant concomitant care permitted or prohibited during the trial

For the subgroup of patients receiving antibiotic decontamination active bacterial infection requiring systemic antibiotics or patients that received IV or oral antibiotics in the past 7 days prior to the planned decontamination will lead to exclusion of this component in these particular patients. Other circumstances that lead to exclusion from antibiotic decontamination are terminal kidney disease or the impossibility to take antibiotic decontamination medication (e.g., vomiting, dysphagia) at time of screening, pregnancy or breastfeeding, emergency or expedited surgery.

### 3.5 Outcomes

The primary endpoint is the CCI at 30 days after the index procedure. The CCI is a continuous scale to measure surgical morbidity that has been developed on the basis of the Clavien Dindo Classification [28] for surgical complications and summarizes and weighs all postoperative complications to a scale from 0 (no complications) to 100 (death of the patient) [27]. This outcome allows to quantify the overall burden of complications and a more subtle detection of differences in the quality of care. It better reflects the patients’ perspective instead of solely summarizing the worst complication the patient did encounter during the course of his or her treatment.

– The first secondary endpoint is the rate of SSI at 30d.– The second secondary endpoint is the mortality rate at 30d.– The third secondary endpoint is the hospital length of stay.– The fourth secondary endpoint is the contribution margin measured as the difference between allocated costs and billed and paid income for a particular case.– The fifth secondary outcome is anastomotic leakage at 30d defined as any radiologically or clinically diagnosed anastomotic leakage.

### 3.6 Participant timeline

For participant timeline see Table 1.

**Table 1 T1:** **a.** Schedule for elective patients. **b.** Schedule for emergency patients.

A. ELECTIVE PATIENTS					

TIME (DAYS)	>–1 DAY	–DAY1	0	+X UNTIL DISCHARGE	+30D

** *Visit* **	*Screening*		*OP*	*In hospital stay*	*Telephone contact* *(or review of chart/contact with treatment team in case of ongoing hospitalization)*

** *oral and written general consent in outpatient clinic or at admission* **	+	+	+		

** *check inclusion-/exclusion criteria* **	*+*				

** *Record preop parameters* **		*+*			

** *Record intraop parameters* **			*+*		

** *Record postop parameters until discharge* **				*+*	

** *Telephone contact for post discharge complications* **					*+*

**B. EMERGENCY PATIENTS**					

**TIME (DAYS)**		**0**	**1–4**	**+x until discharge**	**+30D**

** *Visit* **		*OP*		*In hospital stay*	*Telephone contact* *(or review of chart/contact with treatment team in case of ongoing hospitalization)*

** *oral and written general consent at admission or in case of urgent cases postoperatively* **		*+*	*+*		

** *check inclusion-/exclusion criteria* **			*+*		

** *Record preop parameters* **		*+*			

** *Record intraop parameters* **		*+*			

** *Record postop parameters until discharge* **				*+*	

** *Telephone contact for post discharge complications* **					*+*

### 3.7 Sample size

The sample size calculation described below is for an observational study. Simulations were used to estimate the required sample size. Specifically, we generated 1111 synthetic datasets for a range of potential sample sizes and possible reductions in CCI score due to the modified standard. We then applied the intended analysis (a linear mixed effects model with CCI as the outcome) to each of the simulated datasets. We modelled adoption of the modified standard as a fixed effect and the surgery performance of each study centre as a random effect to account for expected variation in outcomes.

The simulations are based on the following assumptions.

The modified standard will be studied in eight middle sized centres (Clarunis Site Universitätsspital Basel, Kantonsspital Aarau, Spitalzentrum Biel, Kantonsspital Baselland, Luzerner Kantonsspital, Spital Limmattal, Kantonsspital Olten and Lindenhofspital Bern) and one large centre (Clarunis Site St. Claraspital).

We assume that each middle size centre contributes n patients to each condition under study (before and after adoption of the CB) and that Clarunis Site St. Claraspital contributes 2 × n patients to each study condition.

The average CCI score pre-modified standard is 30 with a standard deviation of 12.5 [27].

The standard deviation for surgery outcomes among the centres under study is 20 (based on mortality data from the participating study centres provided by the Swiss Federal Office of Public Health) [8].

We assess the change in CCI using a linear mixed model with CCI after 30 days as the outcome variable, CB implementation as a binary factor and study centre as a random effect. The hypotheses are tested applying a one-sided Wald test for the regression coefficient estimated for the CB factor at the 2.5% Level and a target power of 90%.

Assuming that the CB improves CCI scores by 10 points, 5 patients are needed for each study condition from each middle-sized study centre and 10 patients for each study condition from St. Claraspital. Thus, at least 10 patients should be recruited from each small study centre and 20 patients from St. Claraspital for a combined total sample of 90 patients. This sample size allows detection of an improvement on the CCI with 90% probability (power), assuming that the CB really does reduce the CCI by 10 points on average. As the study is not randomized, the models will include all potential confounders of the true association between the intervention and the outcomes in the final models. To accurately estimate this association the sample size needs to be increased by a variance inflation factor (VIF) that reflects the correlation between the intervention and the confounding factors [29]. As this is difficult to quantify, a conservative VIF of 3.3 was applied to the estimated sample size so that a total of 149 patients per arm and a total of 298 for the study. This target sample size can be realistically achieved within the study period based on current estimated caseloads in the contributing hospitals. This power calculation was performed by the statistical department of the Clinical Trial Unit (CTU) of the Department for Clinical Research of the University Basel and reviewed by an independent statistician. The CTU is a well-established and validated unit. The secondary endpoints as described above will be analysed using descriptive statistics.

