**Highlights:**

**Purpose:**

**Methods:**

**Discussion:**

## 1. Introduction

Complications after colorectal surgery are encountered in up to 40% of patients with anastomotic leakage being the most feared potentially fatal outcome [1,2,3]. Multiple patient factors such as immunosuppression, malnutrition or severe comorbidities as well as surgeon`s and institutional factors such as caseload are known to influence the risk of complications [4,5,6]. While reported overall complication and leak rates showed only minor or no improvements over time, they differ dramatically between institutions, depending on patient`s and surgeon`s selection [5,7]. Surgical Site Infection (SSI) is a key indicator for postoperative complications in colorectal surgery. In North Western Switzerland reported anastomotic leak rates after colorectal resection range from 1.5 to 22% on an institutional level reflecting different case selection as well as surgical practice in the contributing institutions [8].

Recent research showed, that standardization is one possible measure to reduce complication rates in surgery. The introduction of the perioperative WHO Safer Surgery Checklist, for example has shown a reduction of overall operative mortality and morbidity in general surgery for high- and low-income countries [9,10]. While this has led to a widespread implementation of the checklist in most developed countries including Switzerland, only few attempts have been made to improve outcomes by standardizing the peri- and intraoperative process in colorectal surgery so far [11]. J.K. Lovely et al showed, that the implementation of an enhanced recovery pathway including preoperative analgesia, limited intravenous fluids and opiates, and early feeding, led to a significant reduction of hospitalization time in minimal invasive colorectal surgery [12]. One of the most far-reaching changes by standardization in colorectal surgery has been achieved by the introduction of the Enhanced Recovery After Surgery (ERAS) guidelines by the Society for colorectal surgery. This program, which consists of various measures for whose effectiveness there is good evidence, has had a lasting impact on the perioperative management of patients undergoing colorectal surgery [13].

Nevertheless, a number of other interventions have been found to be useful in the reduction of postoperative complications in colorectal surgery involving the following items:

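### The planning values for the CCI (mean 30, SD 12.5) do not fit the protocol's own complication rate, so the stated 90% power at 298 patients is not secured

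*Protocol article*

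**What the plan says.** Section 3.7 bases the simulations on two values for the primary endpoint. The first is "The average CCI score pre-modified standard is 30 with a standard deviation of 12.5". The second is "The standard deviation for surgery outcomes among the centres under study is 20", which the text says comes from mortality data. The test is a "one-sided Wald test for the regression coefficient estimated for the CB factor at the 2.5% Level and a target power of 90" per cent. The power is stated "assuming that the CB really does reduce the CCI by 10 points on average". The requirement is that "5 patients are needed for each study condition from each middle-sized study centre and 10 patients for each study condition from St. Claraspital". The section gives a total of 90 and multiplies by a variance inflation factor (VIF) of 3.3 to reach 149 per arm and 298 in all.

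Three other places bear on these values:

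- Section 3.5 describes the CCI as "a scale from 0 (no complications) to 100 (death of the patient").
- Section 1 (Introduction) states: "Complications after colorectal surgery are encountered in up to 40% of patients".
- Section 7 (Discussion) gives the same ceiling of 40%, but for major complications after colorectal cancer surgery.

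**The concern.** The CCI has a large point mass at 0, because every patient without a complication scores 0. The share of such patients limits which pairs of mean and SD can occur. A mean of 30 with an SD of 12.5 describes a population in which nearly everyone has some complication. The Introduction describes one in which most patients have none.

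Section 3.7 holds the only power statement for the primary endpoint. If the true SD is well above 12.5, a non-significant result at 298 patients could be read as evidence against a 10-point effect when the trial had much less than 90% power to find it. The size of the effect is also in question: at a complication rate of 40%, a 10-point drop may be a large part of the whole baseline mean, or nearly all of it.

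**Working it through.** **Inputs.** From section 3.7: mean 30, SD 12.5, centre SD 20, difference 10, one-sided alpha 2.5%, power 90%, VIF 3.3, 298 patients. From section 3.5: CCI 0 without complications. From section 1: at most 40% with complications. From section 2.1: yearly caseloads.

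**1. The plan's own figure.** A centre random intercept largely cancels from a before-after contrast when each centre contributes equally to both periods. The two-sample formula is therefore a fair check:

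n per arm = 2 × (1.96 + 1.2816)² × 12.5² / 10² = 32.8, so 33.

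The stated 45 per arm gives power Φ(10 / (12.5 × √(2/45)) − 1.96) = 96.7%. Inflation gives 45 × 3.3 = 148.5, rounded to 149 per arm, or 298. So 298 is not reproduced exactly, but it is sufficient if SD 12.5 is right. (Separately, the per-centre counts sum to 8 × 10 + 20 = 100, not 90. The point made here does not depend on that.)

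**2. What the zeros imply.** If a share p of patients has CCI above 0 and the overall mean is μ, those patients average μ/p. The SD is smallest when they all have the same score:

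SD ≥ μ × √((1 − p)/p).

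- At p = 0.40 and μ = 30, patients with complications average 30/0.40 = 75, and SD ≥ 30 × √(0.6/0.4) = 36.7.
- A lower rate makes it worse. At p = 0.30, SD ≥ 30 × √(0.7/0.3) = 45.8.
- For μ = 30 and SD 12.5, p must be at least 1/(1 + (12.5/30)²) = 0.852.
- If 12.5 is the within-centre SD, the total SD is √(12.5² + 20²) = 23.6, and p must be at least 900/(900 + 556.25) = 0.618.
- Turned round, at p = 0.40 and total SD 12.5 the mean cannot exceed 12.5 × √(0.4/0.6) = 10.2. With total SD 23.6 the limit is 19.3.

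**3. Power at 298 for a 10-point difference.** Effective patients per arm are 149/VIF. Power = Φ(10 / (SD × √(2 × VIF/149)) − 1.96), with the same SD in both arms:

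| Common SD | VIF 3.3 | VIF 2 | VIF 1 |
|---|---|---|---|
| 12.5 | 97% | >99% | >99% |
| 20 | 66% | 86% | 99% |
| 25 | 48% | 69% | 93% |
| 36.7 | 25% | 38% | 65% |

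The largest common SD that keeps 90% power is 14.7 at VIF 3.3 and 26.6 at VIF 1.

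The last row can be softened. Taking the centre variance out of 36.7 leaves √(36.7² − 20²) = 30.8 and gives 34% at VIF 3.3. If the treated-arm variance also shrinks because severity falls, power reaches about 51%.

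**4. If all cases are analysed.** The caseloads are 350 + 120 + 200 + 85 + 270 + 100 + 85 + 80 + 125 = 1,415 a year, or about 707 per six-month period before any refusals of consent. At VIF 3.3 that is about 214 effective patients per arm. Power for 10 points is then about 98.5% at SD 25 and about 80% at SD 36.7.

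**The case against.** The strongest reply is that the 40% is a background figure from the literature. It is not a planning input or a rate measured in these nine hospitals, and the Discussion ties it to major complications only. The CCI counts all complications, so the share above 0 need not be capped at 40%. This stands, and it is why a reader who concludes that mean 30 with SD 12.5 is simply impossible goes too far. What remains is that the pair needs some complication in about 85% of patients, or about 62% on the within-centre reading, and the article gives no rate near either. The Introduction and the Discussion also disagree about what the 40% counts.

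A second reply is that the low power figures take 3.3 as the true loss of precision, whereas section 3.7 calls it conservative and hard to quantify. That also stands. Power under the plan's own inputs is 96.7%, and at VIF 1 it stays above 90% up to SD 26.6. A reader might infer that the 90% is false, or that 25% is the true power. The documents fix neither, because they do not show which input is wrong.

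A third reply is that all eligible resections are screened over fixed six-month periods and no stop at 298 is stated, so the analysed number may be far larger. This reduces the harm considerably for a 10-point target, but the article does not say that all cases will be analysed.

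Two further observations add little. Using CCI above 30 as the higher-risk category does not contradict a mean of 30. A centre SD of 20 around that mean does imply some negative centre means, but the intercept largely cancels from the comparison. The mortality source of that SD is a matter of clarity.

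**Conclusion.** The point holds as an inconsistency among planning statements, with a conditional effect on power. Taking the Introduction's rate as any complication, mean 30 and SD 12.5 cannot both be right, since the SD would have to be at least 36.7. Taking it as major complications, they can both be right only at an overall complication rate that the article does not support.

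The 90% power at 298 is therefore not secured. With VIF 3.3 it needs a common SD of no more than about 14.7, and power is about 66%, 48% and 25% at SD 20, 25 and 36.7. At VIF 1 the last two become about 93% and 65%. If the rate of 40% and SD 12.5 are kept and the mean gives way, the mean is at most about 10.2, so a 10-point reduction would abolish nearly all complications. (With a total SD of 23.6 the limit is 19.3, and the reduction would be more than half of the baseline mean.)

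These figures rest on a normal-approximation test with equal arms and a common SD, and on the protocol's VIF as a multiplier of the sample size. SD 20 and SD 25 are illustrations, not values from the article.

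**What to change.** - Reconcile the Introduction, section 3.7 and the Discussion: say whether the 40% is any or major complication, and give the overall complication rate, CCI mean and CCI SD expected in these hospitals as one coherent set. State whether 12.5 is a total or a within-centre SD.
- Re-run the simulation with a zero-inflated CCI bounded to 0–100 and a centre SD expressed on the CCI scale.
- Restate the power, or the detectable difference, at 298 over a range of SD and VIF.
- State that 298 is a minimum and that all consecutive consented eligible cases in both six-month periods are analysed.

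The cost is a repeat of the simulation and some protocol wording. No extra screening or recruitment period is needed, since all cases are already screened. The downside is that the stated power at 298 will probably look less favourable.

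### Section 3.7: the stated inputs give about 97 to 98% power for the base sample, not 90%, and four patients per middle-sized centre would already pass 90%

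*Protocol article*

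**What the plan says.** Section 3.7 of the protocol article derives the sample size by simulation, with 1111 synthetic datasets for a range of sample sizes and effects. It lists these assumptions:

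- Outcome: "The average CCI score pre-modified standard is 30 with a standard deviation of 12.5".
- Centres: "The standard deviation for surgery outcomes among the centres under study is 20".
- Allocation: "each middle size centre contributes n patients to each condition under study", with twice that number at the one large centre.
- Model: a linear mixed model with "CB implementation as a binary factor and study centre as a random effect".
- Test: a "one-sided Wald test for the regression coefficient estimated for the CB factor at the 2.5% Level and a target power of 90" percent.

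The effect is a reduction of 10 points in the CCI. From these inputs the section concludes that "5 patients are needed for each study condition from each middle-sized study centre and 10 patients for each study condition from St. Claraspital". It gives the combined total as 90 patients and says of it: "This sample size allows detection of an improvement on the CCI with 90% probability (power"). A variance inflation factor (VIF) of 3.3 for confounder adjustment then leads to 149 patients per arm and 298 in total.

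**The concern.** The printed assumptions are specific enough to check the printed result, and the two do not agree. Equal numbers before and after within each centre make the bundle effect a within-centre contrast. A random centre intercept then drops out, and precision depends only on the residual SD of 12.5 and the number per condition. With a 10-point effect that contrast is much easier to detect than 90% power at 5 per centre suggests.

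What is at stake is whether the planning assumptions can be read at face value. If the simulation used the inputs as printed, the stated power and the stated minimum number per centre are both wrong. If it used something else, the article gives readers the wrong or incomplete assumptions for the primary endpoint.

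**Working it through.** **Inputs, all from section 3.7.** Effect 10; SD 12.5; centre SD 20; eight centres with n and one with 2n per condition; one-sided 2.5% (z = 1.96); target power 90% (z = 1.2816). The 12.5 must be a within-centre SD, because a total SD of 12.5 cannot contain a centre component of 20.

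**Numbers per condition.** At n = 5: 8 × 5 + 10 = 50, or 100 in total. The printed total of 90 corresponds to 45 per condition. Both are carried below. The mismatch between 90 and 100 is a separate matter and does not affect the conclusion.

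**The step that reproduces.** 45 × 3.3 = 148.5, rounded up to 149 per arm, or 298 in total. The target therefore rests on the printed 90. Starting from 5 per centre would give 50 × 3.3 = 165 per arm, or 330.

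**The step that does not.** With balance within centres, SE = 12.5 × √(2/N) and power = Φ(10/SE − 1.96), where N is the number per condition.

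| Base | N per condition | SE | 10/SE − 1.96 | Power |
|---|---|---|---|---|
| n = 3 | 30 | 3.23 | 1.14 | 87% |
| n = 4 | 40 | 2.80 | 1.62 | 94.7% |
| printed total of 90 | 45 | 2.64 | 1.83 | 96.7% |
| n = 5 | 50 | 2.50 | 2.04 | 97.9% |

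The number for 90% is N = 2 × (1.96 + 1.2816)² × 12.5² / 10² = 32.8, so 33 per condition. On the n/2n scheme the smallest sufficient value is n = 4.

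**Check by simulation.** Fitting the stated mixed model to 1111 datasets per setting (centre SD 20, residual SD 12.5) gave 87.6%, 95.4% and 98.1% for n = 3, 4 and 5, and 97.2% at 45 per condition. A version with centre as a fixed effect and 20,000 datasets gave 86.9%, 94.3% and 97.9%, and 96.7% at 45. At 90% power the Monte Carlo standard error with 1111 datasets is √(0.9 × 0.1/1111), about 0.9 percentage points. The gap is 7 to 8 points.

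**Bounded scores.** With scores truncated to 0–100 the fixed-effect version gave about 84%, 92% and 96% for n = 3, 4 and 5, and 95% at 45 per condition. Four per centre still suffices.

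**Other readings, at 50 and 45 per condition.**

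- Two-sided 2.5%: 96.1% and 94.0%.
- One-sided 5%: 99.1% and 98.4%.
- SD 20: 71% and 66%.
- Combined SD √(12.5² + 20²) = 23.6: 56% and 52%.

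None returns 90%.

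**What would return about 90%.**

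- A residual SD of 10 / [(1.96 + 1.2816) × √(2/50)] = 15.4, or 14.6 with 45 per condition.
- A bundle effect varying between centres with an SD of about 5. The variance of the effect is then 2 × 12.5²/n + 25 in each middle-sized centre, with 2n in place of n at the large one. Pooling by inverse variance gives 91% at n = 5 and 86% at n = 4.

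Section 3.7 states neither.

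**Power at the final target.** With the VIF applied in full, SE = 12.5 × √(2 × 3.3/149) = 2.63, and 10/2.63 − 1.96 = 1.84, so power is about 97%.

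**The case against.** The strongest reply is that a journal article does not list everything a simulation contains. Section 3.7 does not give the distribution of the scores, whether they were bounded, whether the bundle effect varied by centre, or which values of n were tried. If n moved in steps of 5 (an assumption), 5 would be the first value to meet the target, and the 90% would be a threshold passed rather than a power achieved. If the bundle effect varied between centres with an SD of about 5, then 5 per centre would be the smallest sufficient n, at about 91%.

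This limits what can be concluded: the documents do not show whether the simulation or its description is at fault. It does not rescue the text. Each explanation needs an input that the section does not state, and the wording gives 5 as the number needed and 90% as the probability of detection, not as a lower bound.

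It is also fair to say that little depends on the figure operationally. The caseloads in section 2.1 add up to 1,415 a year, or about 700 per six months before losses to consent, and the VIF of 3.3 is itself described as hard to quantify.

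Three stronger readings are tempting and should be resisted:

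- **That the trial is underpowered at 298.** It is not on these inputs, and the article attaches its 90% to the base sample before inflation, not to 298.
- **That the wrong per-centre number produced the 298.** The target comes from the printed 90.
- **That the centre SD of 20 can never matter.** It cancels in an unbounded random-intercept model. With scores truncated to 0–100, power at n = 4 was 94.5% with a centre SD near 0, 92% with 20 and 89.5% with 30.

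**Conclusion.** The point holds as an error in the stated figures, in the conservative direction. The printed power is too low by about 8 percentage points at 50 per condition and about 7 at 45, and the stated minimum of 5 per middle-sized centre is one more than the inputs require. This assumes that 12.5 is the within-centre SD, that the bundle effect is the same in every centre, and that before and after numbers are equal within centres, as printed. Truncating the scores reduces the gap but does not close it. The defect lies in the reported calculation and not in the size of the trial.

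**What to change.** Rerun the simulation and correct section 3.7 in one of two ways:

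1. If the inputs are as printed, replace the 90% with the power they give (about 97 to 98% for the base sample, depending on whether it is 90 or 100 patients, and about 97% at 149 per arm with the VIF of 3.3). Stop describing 5 per middle-sized centre as the number needed for 90%.
2. If a different assumption was simulated, state it with its value so that 5 per centre and 90% follow from the text.

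In either case, say whether simulated scores were bounded at 0 and 100. The cost is one rerun of an existing simulation and a few reworded sentences, with no extra patients and no change to the design.

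### The combined sample of 90 contradicts the per-centre numbers, which sum to 100, and the discrepancy carries into the target of 298; the figures need reconciling

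*Protocol article*

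**What the plan says.** All the figures stand in Section 3.7 (Sample size) of the protocol article.

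- Centres: "The modified standard will be studied in eight middle sized centres", which are then listed by name, "and one large centre (Clarunis Site St. Claraspital").
- Allocation: each middle-sized centre gives n patients per condition (before and after the bundle), while "Clarunis Site St. Claraspital contributes 2 × n patients to each study condition".
- Result of the simulation for a 10-point reduction in the Comprehensive Complication Index (CCI): "5 patients are needed for each study condition from each middle-sized study centre" and "10 patients for each study condition from St. Claraspital".
- Totals over both conditions: for the middle-sized centres, "at least 10 patients should be recruited from each small study centre"; for the large centre, together with the overall sum, "20 patients from St. Claraspital for a combined total sample of 90 patients".
- Inflation: a VIF of 3.3 is applied to allow for confounder adjustment, "so that a total of 149 patients per arm and a total of 298 for the study".

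The section gives a power of 90% for this size, with a one-sided Wald test at 2.5%. Section 2.1 also lists nine hospitals, so the number of centres is consistent across the article.

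**The concern.** The combined total does not follow from the centre count and the per-centre numbers printed beside it. It is not an isolated misprint, because the next step uses it: the final target of 298 is built on 90. That target is the trial's stated recruitment commitment, and a reader who applies the stated rule to the stated design does not arrive at it. At least one of five figures (number of middle-sized centres, patients per centre, combined total, VIF, final target) must therefore be wrong or out of date.

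**Working it through.** **Inputs (all from Section 3.7 unless noted).** Eight middle-sized centres and one large; n = 5 per condition per middle-sized centre and 2n = 10 at St. Claraspital; two conditions; VIF 3.3; difference 10 CCI points; SD 12.5; one-sided 2.5%; target power 90%. Annual caseloads come from Section 2.1.

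**1. The plan's own chain from 90 onwards.** 90 / 2 = 45 per condition. 45 × 3.3 = 148.5, rounded up to 149 per arm. 2 × 149 = 298. This reproduces the printed target exactly, so 298 was derived from 90.

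**2. The step before it.** Total = 2 × (8 × 5 + 1 × 10) = 8 × 10 + 20 = 100, that is 50 per condition. The printed 90 is not reproduced.

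**3. What would give 90.**
- Seven middle-sized centres plus St. Claraspital: 7 × 10 + 20 = 90.
- Nine equal centres: 9 × 10 = 90.

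The first contradicts the list of eight named centres. The second contradicts the double contribution of St. Claraspital.

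**4. The stated rule on the stated design.** 50 × 3.3 = 165 per arm; 2 × 165 = 330. Difference: 330 − 298 = 32 patients, which is 32 / 330 = 9.7% of 330 or 32 / 298 = 10.7% of 298. Read the other way, 298 / 100 = 2.98 is the VIF implied if the base is 100.

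**5. Does the slip cost power?** Assume a random centre intercept only, with 12.5 as the within-centre SD. Each centre contributes equally before and after, so the intercept cancels from the comparison and the between-centre SD of 20 plays no part. With m patients per condition, SE = 12.5 × √(2/m) and power = Φ(10/SE − 1.960).

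| Patients per condition | Design | Power, formula | Power, simulated (5,000 runs) |
|---|---|---|---|
| 40 | eight middle-sized, n = 4 | 94.7% | 95.0% |
| 45 | seven middle-sized, n = 5 | 96.7% | 96.4% |
| 50 | eight middle-sized, n = 5 | 97.9% | 97.8% |

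The minimum for 90% is 2 × (12.5/10)² × (1.960 + 1.282)² = 32.8, so 33 per condition. After the VIF, 149 / 3.3 = 45.2 effective patients per arm, for which power is 96.7%.

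**6. Feasibility.** 350 + 120 + 200 + 85 + 270 + 100 + 85 + 80 + 125 = 1,415 left-sided resections a year, about 707 per six-month period before consent and exclusions, against 165 per arm.

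**The case against.** The strongest reply is that nothing of substance hangs on this. The VIF is a judgement that the article itself calls hard to quantify, and 2.98 against 3.3 lies well within that uncertainty. All eligible patients are screened over two fixed six-month periods, so enrolment is not shown to stop at 298. Power on the stated inputs is above 90% either way. All of this stands, and it limits the consequence. It does not remove the contradiction: a printed total disagrees with the numbers beside it, and the main sample-size figure rests on that total.

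Three stronger readings are tempting and are not supported.

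- *The right target is 330.* That holds only if eight centres and n = 5 are both correct. The article does not show which figure slipped. A total left over from seven middle-sized centres is plausible but is an inference. On the listed inputs n = 4 already exceeds 90% power, which would give 40 × 3.3 = 132 per arm and 264 in total, below 298.
- *The per-centre figures of 10 and 20 were wrongly left uninflated.* They come before the VIF step and describe the uninflated calculation. Nothing says that they are the final per-centre minima.
- *The power calculation is wrong because 5 per centre gives 97–98% rather than 90%.* The size came from simulation over a range of sample sizes. The grid and the details of data generation are not given, and a size above the target power is conservative rather than deficient. What remains is a wording point.

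**Conclusion.** The combined total of 90 is wrong as written against the stated design, which gives 100 (50 per condition), and the discrepancy was carried into 149 per arm and 298. With eight middle-sized centres, n = 5 and a VIF of 3.3, the result is 165 per arm and 330: a gap of 32 patients, or 9.7% of 330. The link from 90 to 298 is sound; the failure lies in the link from the per-centre numbers to 90.

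A reader might infer that the trial is underpowered. The article does not support that. With SD 12.5, a difference of 10, one-sided 2.5%, a random centre intercept only and a true VIF of 3.3, a target of 149 per arm still gives about 97% power. The defect is a target that does not follow from its own inputs, not a demonstrated loss of power.

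**What to change.** Reconcile the centre count, patients per centre, combined total and inflated target in Section 3.7, in one of two ways:

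- if eight middle-sized centres and n = 5 stand, restate the combined total as 100 (50 per condition) and the target as 330 (165 per arm); or
- re-run the simulation for the nine centres with the stated 1:2 weighting, and restate n, combined total, inflated target and power together.

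In either case, give the power as at least 90% or as the simulated value for the chosen size.

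The first option is a text correction and the second a short re-run. At about 707 resections per six-month period, the stated caseload covers 165 per arm more than four times (707 / 165 = 4.3) before consent and exclusions, so the recruitment period need not change.
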